## Abstract

**Background:**

The increased prevalence of obesity in pregnant women in Australia and other developed countries is a significant public health concern. Obese women are at increased risk of serious perinatal complications and guidelines recommend weight gain restriction and additional care. There is limited evidence to support the effectiveness of dietary and physical activity lifestyle interventions in preventing adverse perinatal outcomes and new strategies need to be evaluated. The primary aim of this project is to evaluate the effect of continuity of midwifery care on restricting gestational weight gain in obese women to the recommended range. The secondary aims of the study are to assess the impact of continuity of midwifery care on: women's experience of pregnancy care; women's satisfaction with care and a range of psychological factors.

**Methods/Design:**

A two arm randomised controlled trial (RCT) will be conducted with primigravid women recruited from maternity services in Victoria, Australia. Participants will be primigravid women, with a BMI≥30 who are less than 17 weeks gestation. Women allocated to the intervention arm will be cared for in a midwifery continuity of care model and receive an informational leaflet on managing weight gain in pregnancy. Women allocated to the control group will receive routine care in addition to the same informational leaflet. Weight gain during pregnancy, standards of care, medical and obstetric information will be extracted from medical records. Data collected at recruitment (self administered survey) and at 36 weeks by postal survey will include socio-demographic information and the use of validated scales to measure secondary outcomes.

**Discussion:**

Continuity of midwifery care models are well aligned with current Victorian, Australian and many international government policies on maternity care. Increasingly, midwifery continuity models of care are being introduced in low risk maternity care, and information on their application in high risk populations is required. There is an identified need to trial alternative antenatal interventions to reduce perinatal risk factors for women who are obese and the findings from this project may have application in other maternity services. In addition this study will inform a larger trial that will focus on birth and postnatal outcomes.

**Trial Registration:**

**Australian New Zealand Clinical Trials Registry **ACTRN12610001078044.

## Background

Obesity in pregnancy has increased to epidemic proportions in developed countries; it is associated with adverse outcomes for both mother and child [1] and is one of the most commonly occurring risk factors in maternity care [2]. Recent estimates suggest that approximately 35% of pregnant women in Australia have a body mass index (BMI) of greater than 25 kg/m^2 ^[3]. Maternal obesity is a well recognised perinatal risk factor [4] and it is associated with sub-fertility in women and an increased risk of miscarriage and stillbirth [5]. Maternal risks for hypertensive disorders [3,6-8], gestational diabetes [3,6,9] thrombo-embolism [8], haemorrhage, infections [8] and death [10] are increased in obese women and there are attendant risks and resourcing issues associated with obesity and childbirth. Compared to women who have a BMI between 20.1-25, obese women are more likely to experience: increased rates of induction of labour and a failed induction; anaesthetic difficulties [11-13]; a caesarean section [3,14-16]; a stay in hospital of more than five days [3] and obese women require specific equipment for accurate monitoring and safe maternity care [2]. The risks of adverse outcomes for fetuses and neonates are also increased. Maternal obesity is associated with fetal macrosomia, birth defects, prematurity, higher rates of admission to neonatal intensive care environments [3,12,17] and perinatal death [6,12,17,18]. The impact of obesity is pervasive with maternal obesity also being associated with postnatal effects of lower breastfeeding rates [19] and longer term with obesity in childhood [20]. Higher birth weight babies are associated with adolescent obesity [21] and are more likely to grow into obese adults [20].

In 2009 the American Institute of Medicine (IOM) published revised guidelines on how much weight a woman should gain during pregnancy and highlighted the importance of intervention in pregnancy to prevent *both *postpartum weight retention and childhood obesity [22]. The IOM recommends that women who are obese (BMI of 30 kg/m^2 ^and above) should gain approximately 5 to 9 kg. Excessive gestational weight gain is defined as weight gain above this recommended guideline. A recent systematic review of studies designed to prevent excessive gestational weight gain [23] revealed that, across seven studies, 63-74% of obese women gained more than 9 kg during their pregnancy and therefore exceeded the IOM guidelines for weight gain. Indeed, the adherence to recommended weight gain guidelines appears to be significantly lower for obese, as opposed to healthy weight, pregnant women [24]. There is limited evidence to support the effectiveness of dietary and physical activity lifestyle interventions in preventing adverse perinatal outcomes. In a systematic review of nine trials involving 743 women, Dodd and colleagues [25] concluded that the effectiveness of antenatal lifestyle interventions remain unclear. This is of significant concern and forms the rationale for trialling a different approach to preventing excessive weight gain in obese women.

Maternity reform at both federal [26] and state [27] levels of government promote the benefits of continuity of care and the expanded role of midwives working collaboratively in multidisciplinary teams. Continuity of care can be defined as care that is provided by the same clinician or small group of clinicians throughout pregnancy, birth and the postnatal period [28,29] and is often used in the context of models of midwifery care. There is evidence from a systematic review involving 11 trials and 12,276 women [30] that supports the beneficial effects of continuity of midwifery care on improving selected outcomes for women with no evidence of adverse outcomes. Hatem et al. propose that the underpinning philosophy of midwife-led care is normality and that caution needs to be exercised where medical complications exist and care needs a multidisciplinary approach [30].

Continuity of midwifery care can empower women and promote participation in their care [29] improve the sense of control they perceive [29,31], and improve satisfaction with care [29,31,32]. However, the impact of continuity of midwifery care as an intervention to improve outcomes for women who are obese has not been explored. It is important that both clinicians and obese women are aware of the need to limit gestational weight gain and participate in additional care, such as additional monitoring, in order to minimise the risk of maternal and fetal complications [2].

Evidence-based care should involve women being actively involved in their care, being provided with accurate information on risks and management in a sensitive manner [2]. In the absence of evidence based Australian guidelines, it is not surprising that currently there is significant variation in the quality and quantity of information that obese women receive in pregnancy. There is a particular science involved in the development of consumer health information where the topics are of a sensitive nature [33,34] in order to assist women to make informed choices. The need to measure continuity of midwifery care as an intervention for obese women is timely with the emergence of more midwifery led models in Australia. Evaluating the effect of a resource that is based on the latest evidence based guidelines is also identified as a significant need in clinical practice.

We plan to evaluate the impact of midwifery continuity of care on restricting gestational weight gain in obese women to the recommended range. Secondary aims of the study are to assess the impact of midwifery continuity of care on women's experience of and satisfaction with care and on a range of psychological factors. This paper describes the trial protocol in detail.

## Methods

This study employs a two arm unblinded randomised controlled trial (RCT) where pregnant women are allocated to either the intervention or control group. The study will be conducted and reported in line with CONSORT recommendations (Additional file 1.)

### Aims

This project has one primary aim: to measure the impact of continuity of midwifery care compared to routine care on restricting excessive gestational weight gain in obese women. Secondary aims are to measure the impact of continuity of midwifery care compared to routine care on obese women's experience of pregnancy care, women's satisfaction with care and selected psychological factors.

### Participants

The participants will be 214 primigravid women who attend one of the recruiting maternity services for pregnancy care (Eastern Health, Barwon Health and Goulburn Valley Health) during the recruitment period and at booking have a BMI≥30 and are less than 17 weeks gestation [8]. Women will be excluded from participating in the study if they: Are unable to give informed consent in English; have a multiple pregnancy; are currently experiencing vaginal bleeding; have a severe medical condition that prevents them from being randomised to a continuity of midwifery care model or have already commenced in a shared-care model of care with their General Practitioner.

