### Power, sample size and retention

A difference between groups of 20% is deemed clinically significant. The proportion of obese women gaining weight in excess of evidence based guidelines is approximately 65% [23]. It is estimated that 107 women per study arm (total of 214 participants) is required in order to detect a difference of 20% between groups with 80% power at a 0.05 level of significance [41]. Based on current booking numbers and the prevalence of obesity at the recruitment sites, approximately 74 women will be eligible to participate each month. To accommodate an anticipated 77% participation rate [42] and a 15% attrition rate [42], the required sample will be recruited in four and a half months.

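### The Participants section gives 214 women as the trial's size, while the power section needs 214 after attrition and its recruitment period implies about 252 to 256 randomised

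*Protocol article*

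**What the plan says.** The number 214 appears twice in the protocol article.

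- **Participants:** "The participants will be 214 primigravid women". The sentence goes on to describe women attending the three services while recruitment is open who meet the BMI and gestation criteria at booking. That describes entry to the trial.
- **Power, sample size and retention:** "107 women per study arm (total of 214 participants) is required in order to detect a difference of 20% between groups with 80% power". Here 214 is what the power calculation needs.

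The power section then gives about 74 eligible women a month, expects 77% of them to take part, and ends by allowing for "a 15% attrition rate [42], the required sample will be recruited in four and a half months". No section prints an enrolment number larger than 214.

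**The concern.** A number required for power is a number with an outcome. A number of participants, in a section on eligibility, is a number enrolled. With 15% attrition expected, the two cannot be equal. The enrolment figure decides when recruitment stops, and a shortfall cannot be repaired at analysis.

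Loss before the primary outcome is plausible. Women enter before 17 weeks, and the outcome needs a weight taken at the service from 36 weeks onwards. A team that took the Participants section literally would stop at 214 and could analyse fewer women than the power statement requires.

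**Working it through.** **Inputs.** From the power section: 65% of obese women exceed the guideline; difference 20 percentage points; power 80%; significance level 0.05; 107 per arm; 74 eligible women a month; participation 77%; attrition 15%. From Analyses: chi-square test on proportions. Assumptions: a two-sided test (sidedness is not stated) and a reduction from 65% to 45%.

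**1. Reproduce 107 per arm.** With p1 = 0.65, p2 = 0.45 and mean 0.55:

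n = [1.960 × √(2 × 0.55 × 0.45) + 0.842 × √(0.65 × 0.35 + 0.45 × 0.55)]² / 0.20² = 95.9, so 96 per arm.

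With the continuity correction:

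n' = (n/4) × [1 + √(1 + 4/(n × 0.20))]² = 105.7, so 106 per arm (212 in total).

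This is within one woman per arm of the stated 107; 60% versus 40% gives 106.7, so 107 exactly. Other readings do not fit:

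- one-sided: 76, or 86 with correction
- 65% versus 85%: 73, or 83 with correction
- a relative 20% reduction (65% versus 52%): 225, or 240 with correction
- the uncorrected 96 inflated for attrition: 96/0.85 = 113

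The likeliest origin of 107 is therefore the continuity-corrected formula with no attrition allowance.

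**2. What the recruitment period implies.**

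- Randomised per month: 74 × 0.77 = 56.98
- Randomised in 4.5 months: 56.98 × 4.5 = 256
- Retained: 256.4 × 0.85 = 218, which meets 214
- Enrolment that leaves 214: 214/0.85 = 251.8, so 252 (126 per arm), taking 252/56.98 = 4.4 months
- Time to enrol only 214: 214/56.98 = 3.8 months

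Four and a half months fits an enrolment of 252 to 256, not 214.

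**3. Power if enrolment stopped at 214 and all 15% lost the primary outcome.** 214 × 0.85 = 181.9, about 91 per arm.

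- Uncorrected: Φ[(0.20 − 1.960 × √(0.495/91)) / √(0.475/91)] = Φ(0.767) = 77.9%; exact enumeration of the chi-square test gives 76.9%
- Continuity-corrected: replace 0.20 by 0.20 − 1/91, giving Φ(0.615) = 73.1%; Fisher's exact test, by enumeration, gives 72.2%

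For comparison, 107 analysed per arm gives 84.2% uncorrected and 80.5% corrected.

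**4. How much loss 214 can bear.** The uncorrected formula needs 96 per arm, or 192. Since 192/214 = 0.897, enrolling 214 keeps 80% power on that basis if no more than about 10% lose the primary outcome. On the corrected basis it needs 212 of the 214.

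**The case against.** The strongest reply is that attrition is already handled. The power section says so, its arithmetic works (218 retained against 214 needed), and no printed figure in that section is wrong. The Participants section may simply repeat the required total, and nothing there tells the team to stop at 214. This stands in part. A reader might infer that the trial will be underpowered, or that its sample size contains a calculation error. The document supports neither: the shortfall arises only if the Participants section governs, and 107 is reproduced closely. What remains is that the section describes women at entry, and that elsewhere participants are the women randomised (under Randomisation Procedure, all of them receive the leaflet).

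Second, 91 per arm is the all-lost case. The primary outcome comes from medical records, not from the posted questionnaire, and attrition is not defined. If part of the 15% is questionnaire non-return, more than 182 women would have a primary outcome. This stands.

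Third, the Analyses section mentions no continuity correction, so 77–78% is the fairer figure for the planned test. This also stands; 72–73% needs a correction that the article never states.

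Fourth, 107 might already include attrition, since an unpooled formula gives 93.2 per arm and 93.2 × 1.15 = 107.2. The text does not support this: attrition comes in after 107 is fixed and is applied to the required sample, and the recruitment period fits only if 214 is inflated again.

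Last, a condensed article may leave an inflated target to the full protocol. That would excuse silence, but the article prints a participant number that disagrees with its own recruitment figures.

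**Conclusion.** The two sections conflict on the enrolment target: 214 in one, about 252 to 256 implied by the other. This is an internal inconsistency of moderate importance. The loss of power is conditional on recruitment stopping at 214 and on the full 15% lacking a primary outcome. The planned test would then fall 2 to 3 points below the stated 80%, and a continuity-corrected analysis 7 to 8 points below. These sizes assume a two-sided test and 65% versus 45%. The reading of 107 as uninflated is an inference, but both the formula and the recruitment period point to it.

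**What to change.** State in both sections that about 252 women (126 per arm) will be randomised so that 214 (107 per arm) have a primary outcome. Say whether the 15% refers to a missing late-pregnancy weight or to unreturned questionnaires.

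The change is one of wording. It means 252 − 214 = 38 more women than the Participants section now names, but the stated four and a half months already allows for them at the plan's own rates.

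If 214 is meant as the number randomised, keep it and restate the power after attrition: about 77–78% for the uncorrected chi-square test if all 15% lack the primary outcome, or 72–73% with a continuity correction. The recruitment period would then need to be reconciled too, since 214 women take 3.8 months at those rates.

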### Recruitment strategies

Information on this study will be posted to all women with their initial appointment. Following the calculation of their BMI at the booking in visit, women eligible to participate will be provided with verbal and written information about this project by the attending doctor or midwife or a research assistant (RA) and invited to participate. Women will be given time to ask questions and will provide written informed consent prior to randomisation.

### Randomisation Procedure

Block randomisation will be undertaken using a computer generated randomisation sequence for each recruitment site. Following the recruitment of each woman, an opaque envelope will be selected in sequential order by the attending clinician and the contents will indicate allocation to the intervention group or the control group.

Women in the intervention group will receive 'continuity of care' defined as seeing the same midwife or small team of midwives for pregnancy care visits.

Women in the control group will receive usual clinical care. This may involve a care in one of any number of models of care available at the maternity service. Within these models of care, women see a variety of clinicians and are likely to see the same midwife at pregnancy care consultations only by chance.

All participants will receive an evidence based informational leaflet developed by the Nutrition and Dietetics Department at Goulburn Valley Health (Additional file 2). This will be modified at other sites to badge the relevant health service logo.

### Blinding

Given the nature of the intervention, blinding of researchers is not practical in this study, however a person independent of the study will keep the master list of all randomised participants and will audit the integrity of the randomisation prior to analysis.

Participating women will provide written consent prior to randomisation. Attrition bias will be minimised by all participants receiving an informational resource.

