### Primary outcome and measures

#### Gestational weight gain

The primary outcome is the proportion of women with a gestational weight gain within IOM guidelines. A medical record review will compare the last weight recorded in pregnancy (taken at the maternity service at 36 weeks onwards and as close as practical to birth) with the woman's booking-in weight (taken at the maternity service when the woman's BMI is calculated).

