### Analyses

Analyses will be undertaken using STATA [43] and comparability of baseline characteristics will be assessed for participants in both groups. The intervention group will be compared to the control group by intention to treat analysis. Proportions of women restricting weight gain to recommended levels will be compared using chi-square tests and odds ratios. Comparison of means will be undertaken for continuous variables using t-tests where data are normally distributed, otherwise medians will be compared using Mann-Whitney U tests. Ranked or Likert scales will be analysed using cumulative odds ratios and 95% confidence intervals will be reported. Where differences in baseline characteristics exist that may be associated with outcomes, additional multivariate analysis will be performed.

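### The reason given for not blinding researchers covers women and treating clinicians, not the analyst or the person who extracts the weights; the likely bias is modest and the remedy is cheap

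*Protocol article*

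**What the plan says.** The Methods section of the protocol article labels the trial unblinded. The Blinding section says that "blinding of researchers is not practical in this study" and gives the nature of the intervention as the reason. The statement makes no exception for the analyst or for the reviewer of the records. The same section arranges that "a person independent of the study will keep the master list of all randomised participants and will audit the integrity of the randomisation prior to" the analysis.

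Under Gestational weight gain, "The primary outcome is the proportion of women with a gestational weight gain within IOM guidelines". It comes from a review of medical records, which compares the booking-in weight with the final weight on record in the pregnancy, "taken at the maternity service at 36 weeks onwards and as close as practical to birth".

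The Analyses section fixes an intention-to-treat comparison of proportions by chi-square test and odds ratio. Continuous variables are compared by t-test or Mann-Whitney U test, depending on whether they are normally distributed. It adds: "Where differences in baseline characteristics exist that may be associated with outcomes, additional multivariate analysis will be performed".

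According to Data Collection, the record audit that yields the weights also counts the clinicians each woman saw.

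**The concern.** The stated reason is narrower than the conclusion drawn from it. A model of care cannot be hidden from the woman or her midwife. It can be hidden from someone who receives a data file with arms A and B, and largely from someone who transcribes two weights and their dates without the allocation list. The protocol already has an independent person holding the master list, but uses that person only to keep the list and audit the randomisation.

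Knowledge of the arm could act in three places:
- in extraction, where the last service weight falls before 36 weeks, lies well before the birth, or is missing;
- in the choice between t-test and Mann-Whitney for continuous outcomes;
- in deciding which baseline differences call for an adjusted analysis, since no covariates are named.

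At stake is mainly the credibility of the secondary and adjusted results and, to a smaller degree, of the primary result.

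**Working it through.** **1. Whom does the reason cover?**

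| Person | Does the nature of the intervention prevent masking? | Where the documents bear on it |
|---|---|---|
| Woman | Yes | Randomisation Procedure: she sees one midwife or a small team, or a variety of clinicians |
| Treating clinician | Yes | Same section |
| Clinic staff who measure the final weight | In practice yes | Gestational weight gain: the weight is taken at the maternity service |
| Person who extracts the weights | No, though the record may show the care model | Gestational weight gain; Data Collection |
| Analyst | No, unless given a variable that reveals the arm | Analyses; Data Collection (count of clinicians) |

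The booking weight is measured when BMI is calculated. Recruitment strategies and Randomisation Procedure place this before consent and allocation, so its measurement is not at risk.

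**2. The plan's own figure.** Power, sample size and retention gives 107 per arm for 65% against 45%, 80% power, level 0.05 (two-sided assumed). The two-proportion formula with continuity correction gives 106, and without correction 96. So 107 reproduces to within one woman. Masking enters none of these inputs, and the figure stays as it is.

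**3. A yardstick for the primary outcome.** From the documents: 65% of women exceed the guideline (sample size section), and the guideline for obese women is about 5 to 9 kg (Background). Assumed, because the documents do not give them: normally distributed gain, SD 5, 6 or 7 kg, and a systematic shift d of 0.3 to 1.0 kg in one arm (one to two weeks at 0.3 to 0.5 kg per week).

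- Mean gain: μ = 9 + 0.385 × SD, which puts 65% above 9 kg. This gives 10.93, 11.31 and 11.70 kg.
- Density at the upper limit: φ(0.385)/SD = 0.3704/SD, or 7.4, 6.2 and 5.3 points per kg.
- Density at the lower limit: φ((5 − μ)/SD)/SD, or 3.9, 3.8 and 3.6 points per kg.
- Proportion within range: W(μ) = Φ((9 − μ)/SD) − Φ((5 − μ)/SD). Change for a downward shift: W(μ − d) − W(μ).

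| SD (kg) | Change in proportion within 5–9 kg, d = 0.3 | d = 1.0 |
|---|---|---|
| 5 | 1.0 points | 3.2 points |
| 6 | 0.7 points | 2.2 points |
| 7 | 0.5 points | 1.6 points |

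The change is small because women who drop below 9 kg are partly offset by women who drop below 5 kg.

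**4. What a bias of this order does to the test.** Assume 35% in both arms, 107 per arm, and an uncorrected two-sided 0.05 test. A spurious 2-point gain for one arm raises the chance of a significant result from 5% to about 6%. A 5-point bias would raise it to about 12%, but 5 points lies outside the range in step 3.

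**The case against.** The other side has a strong case, and most of it stands.

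- **The extractor has little choice.** The protocol already names the final recorded weight. The words about 36 weeks and closeness to birth can be read as saying when that weight is taken. Judgement remains only at the edges: a last weight before 36 weeks, long before birth, or missing.
- **The primary test leaves the analyst little room.** It is a chi-square test by intention to treat. The normality decision concerns continuous outcomes, and the adjusted analysis is additional. Coding the arms does not stop covariates being chosen after a look at the data. Only pre-specification does, and that may sit in an analysis plan not shown here.
- **Masking can fail.** An analyst who receives the count of clinicians could tell the arms apart, because that count reflects the contrast under test.
- **The trial openly calls itself unblinded, and the outcome is a measured weight.**

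A reader might infer that unmasked choice of the final weight could move 2 to 7 points of women across the guideline limit. The documents do not support this. That figure multiplies the density at 9 kg by 0.3 to 1.0 kg, and so ignores the 5 kg limit of an outcome defined as gain within the guideline. A one-to-two-week gap between the arms' last weights would also come mostly from visit timing, which masking does not remove.

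None of this rescues the blanket statement. Its reason still does not reach the analyst or the extractor.

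**Conclusion.** The concern holds in a limited form. The Blinding section excludes all researchers from blinding for a reason that applies only to women and treating clinicians. This is a stated decision with an insufficient reason, not a detail left to another document.

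The likely bias is modest. On the 5 to 9 kg range, a 0.3 to 1.0 kg shift is worth about 0.5 to 3 points against the 20-point target. That rests on a normal distribution, an assumed SD of 5 to 7 kg and 65% above 9 kg. It shows how sensitive the outcome is; it does not estimate what masking would prevent, which the documents do not allow to be sized.

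A reader might also infer that the primary result is open to manipulation, or that analyst masking would be complete. Neither follows: the weight and the test are largely fixed, and masking of the analyst depends on withholding care-model variables. The case for change is that the safeguard is cheap and the person needed for it is already in the plan.

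**What to change.** 1. In Blinding, limit the statement to the women and their treating clinicians, and say who will be masked.
2. Have the independent list-holder release the arms as A and B. The code stays closed until the primary analysis is done and the choices that Analyses leaves open are recorded: the test for each continuous outcome and the covariates of the adjusted analysis. Until then, keep the count of clinicians and other care-model variables out of the analyst's file.
3. Extract the booking weight and the last dated service weight first, with their dates, on a form that carries only the study number. The extractor does not hold the allocation list. Standards of care and care-model items follow on a second form.

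The cost is a change of wording, a two-part extraction form, and a coded data file released in two steps. The documents do not say whether the sites have someone without knowledge of the allocation to extract the weights, so this needs checking. Two limits remain and should be stated: extraction masking is partial because the record may show the model of care, and clinic staff who measure the final weight stay unblinded. Sample size, significance level and power are unaffected.
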